### 2.5. Data analysis

#### 2.5.1. Effectiveness.

Baseline characteristics will be summarized using appropriate descriptive statistics (e.g., means and standard deviations or medians and interquartile ranges for continuous variables, and frequencies and percentages for categorical variables). Within the intervention group, pre-post changes over time will be evaluated using paired t-tests or non-parametric equivalents when assumptions are not met. Given the non-randomized and exploratory nature of the study, analyses comparing the intervention and control group will primarily be descriptive and exploratory. Potential baseline differences between groups will be taken into account by exploring propensity score-based approaches, such as inverse probability of treatment weighting (IPTW), if deemed feasible given the sample size and data distribution. Outcome differences between groups will be interpreted cautiously, with emphasis on effect sizes and confidence intervals rather than formal hypothesis testing alone. All statistical tests will be two-sided, and statistical significance will be set at p < 0.05. Missing data will be reported and handled transparently; given the expected small sample size, no multiple imputation procedures are planned.

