**Fig 3 pone.0353932.g003:**
[figure not shown]
Overview of the quasi-experimental pre-test post-test study.

Participants in the intervention group will receive the TP over 13–16 months, depending on the trajectory specific to their condition. Questionnaire assessments will be administered at three time points: at baseline, prior to the start of the intervention (T0); at the time of transfer to adult care services (T1), with the questionnaire completed immediately after the last consultation on paediatric care services; and four months post-transfer (T2). For the control group, whom receive usual care, assessments will be conducted at the time of transfer (T1), with the questionnaire completed immediately after the last consultation on paediatric care services, and four months post-transfer (T2).

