#### 2.3.2. Participants.

The study will focus on three common chronic childhood-onset conditions: type 1 diabetes, asthma, and obesity. The three diagnostic groups will be included to ensure variability and representativeness. Eligibility criteria for the intervention group include: being 17 years old, having a diagnosis of one of the target conditions, at least one paediatric outpatient visit in the past 12 months, Dutch-speaking, and a planned transfer to adult care within 12 months. Participants in the control group are aged 17,5–18 years, Dutch-speaking, with a planned transfer to adult care in the near term. Patients with severe mental, cognitive, and/or neurological impairments are excluded. At UZ Ghent, only type 1 diabetes patients will be included, while at UZA, patient with asthma and obesity patients will be included.

Based on reference data from previous studies, the intervention target was defined as an improvement in the primary outcome corresponding to a one standard deviation (SD) increase in the TRAQ score [24–26]. This target was set assuming 90% power, an effect size of d < 0.6, and a significance level of α = 0.05. A power analysis conducted using G*Power 3.0 indicated that 22 participants per group (intervention and control) would be required. Considering the heterogeneity of the AYA population and comparable disease complexity across subgroups, this sample size was applied at the population level, resulting in a total required sample of 44 participants. To account for an anticipated attrition rate of 25% over a 24-month follow-up period [27], as well as potential recruitment challenges, the total target sample size was increased to 55 participants. Accordingly, a minimum of 28 participants per group (intervention and control) should be recruited.

For the process evaluation, all participating AYAs, their families, and involved healthcare providers will be invited to complete quantitative assessments. A purposive subsample will be selected for qualitative evaluation to capture variability in experiences and perspectives, ensuring representation across conditions, sites, and roles in the care process.

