**EQ-5D-5L.** Self-perceived health status is measured using the EQ-5D-5L [32], a standardised instrument covering five dimensions (mobility, self-care, usual activities, pain/discomfort, and anxiety/depression). Each dimension is rated across five levels of severity, ranging from no problems to extreme problems. Responses define a specific health state that can be converted into a utility score using country-specific value sets. Additionally, it includes a visual analogue scale (VAS), where AYAs to rate their overall health on a scale from 0 (worst imaginable health) to 100 (best imaginable health).

**Hospital Anxiety and Depression Scale (HADS).** Symptoms of anxiety and depression are assessed using the HADS [33], a 14-item instrument designed for use in clinical populations. It consists of two subscales: anxiety (seven items) and depression (seven items). Each item is scored on a 4-point scale, resulting in subscale scores ranging from 0 to 21. Higher scores indicate higher levels of anxiety or depressive symptoms. The HADS is commonly used because it focuses on psychological symptoms while minimizing the influence of physical illness.

At baseline, data will be collected using a paper-based questionnaire. This approach allows the researcher to be present during completion, providing clarification and support in case participants experience difficulties or have questions. At subsequent time points, questionnaires will be administered electronically via a secure online survey platform (i.e., REDCap) and distributed through an automated email system. To maximize response rates, reminder emails will be sent to participants who have not completed the questionnaire within a predefined timeframe. The questionnaire was pilot tested internally by the research team to evaluate its feasibility and acceptability. Specifically, the pilot evaluation focused on readability, comprehensibility of the items, and overall completion time. On average, completion of the questionnaire takes approximately 10–15 minutes, indicating an acceptable respondent burden.

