Despite these strengths, several limitations should be acknowledged. First, the quasi-experimental design without randomization may introduce selection bias. To address this, IPTW will be used to balance observed covariates between groups, however, this approach does not account for unobserved confounders [50,51]. Second, the study relies on self-reported measures, which may introduce reporting bias and social desirability effects [52,53]. However, the use of validated instruments such as the TRAQ 6.0, GYPES, MARS-5, EQ-5D-5L, and HADS strengthens the reliability and comparability of findings [54]. In addition, the relatively short follow-up period of four months post-transfer may not fully capture long-term outcomes, such as sustained adherence, disease control, or healthcare utilization patterns [55]; nevertheless, it does fully cover transition’s most critical point of healthcare continuity, i.e., the transfer. The embedded process evaluation, however, will help interpret findings and identify barriers and facilitators. As transition is inherently a longitudinal process, future studies should include longer follow-up periods to evaluate the durability of effects. Due to time constrains within the current project, this was not feasible. Implementation across multiple centres and conditions may also introduce contextual variability, including differences in organizational structures, care practices, and resource availability [56]. While this heterogeneity may complicate interpretation findings, it is also a strength in terms of external validity. The embedded process evaluation will be crucial to understand how contextual factors influence implementation, identify barriers and facilitators, and explain observed outcomes.

Importantly, this study positions TPs within the broader framework of the sextuple aim of healthcare, aiming to improve patient outcomes and experiences, support healthcare providers, optimize costs, and indirectly promote health equity and environmental sustainability [57]. The inclusion of healthcare providers’ perspectives acknowledges that successful implementation depends not only on patient engagement but also on provider workload, interprofessional collaboration, and organizational support.

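### The only test the plan names is an uncontrolled pre-post test in the intervention group, while the two-group comparison that fixed the sample size is left mainly descriptive, so natural change can be read as a programme effect

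*Protocol article*

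**What the plan says.** All places are in the protocol article.

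- **Analysis (2.5.1).** "Within the intervention group, pre-post changes over time will be evaluated using paired t-tests or non-parametric equivalents when assumptions are not met". For the other comparison, "analyses comparing the intervention and control group will primarily be descriptive and exploratory". Group differences are to be read cautiously, "with emphasis on effect sizes and confidence intervals rather than formal hypothesis testing alone". Tests are two-sided at 0.05. Propensity weighting (IPTW) is to be explored "if deemed feasible given the sample size and data distribution", whereas the Discussion (section 3) says that "IPTW will be used to balance observed covariates between groups".
- **Sample size (2.3.2).** The target is a 1 SD gain in TRAQ with 90% power, alongside a stated effect size below 0.6. The result is that "22 participants per group (intervention and control) would be required".
- **Assessments (2.3.1, text under Fig 3).** The intervention group is measured at T0, T1 and T2. "For the control group, whom receive usual care, assessments will be conducted at the time of transfer (T1") and again four months later. No control T0 is planned.
- **Mode (2.4.1).** "At baseline, data will be collected using a paper-based questionnaire", with the researcher present. Later questionnaires are electronic and sent by email.
- **Use of results (section 3).** Preliminary effect sizes are among the parameters to be handed to a future larger evaluation.

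**The concern.** The study is sized for a contrast between two groups, but the one test that the plan names uses one group. Those participants enter at 17 and are followed to transfer at about 18 and then to T2, with the programme running 13–16 months. TRAQ measures skills such as managing medication and keeping appointments, which may grow with age and as transfer approaches, whether or not there is a programme. The change in questionnaire mode falls at the same point as the passage of time, so the paired difference combines programme, age and mode. Without a control T0, nothing in the data can separate them.

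Two things are at stake. A significant paired result could be taken as evidence for the programme. The within-group change could also be carried into the next trial as its expected effect, which would make that trial too small. The plan acknowledges age-related selection between groups (2.3.3) and self-report bias (section 3), but it nowhere names natural change or mode as a threat to the pre-post test.

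**Working it through.** **Step 1. Which comparison does 22 per group belong to?** Inputs from 2.3.2 and 2.5.1: power 0.90, two-sided alpha 0.05, equal groups.

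Two independent means, normal approximation: n per group = 2(1.960 + 1.282)²/d².
- d = 1.0: 2 × 10.51 = 21.02, rounded up to 22. The exact t calculation gives 22.02, and power at 22 per group is 89.97%.
- d = 0.6: 21.02/0.36 = 58.4, rounded up to 59 (60 by the exact t calculation). Power at 22 per group is 49%; at the recruitment target of 28 it is 60%.

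Paired test, exact t, same power and alpha:
- standardised change 1.0: 13 pairs
- standardised change 0.6: 32 pairs

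So 22 is reproduced by the two-group comparison at 1 SD and by neither paired calculation. The plan's other figure, an effect size below 0.6, does not lead to 22.

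**Step 2. How often would the paired test reject with no programme effect?** The documents give neither the natural gain nor the T0-to-follow-up correlation, so both are assumed. Let m be the natural TRAQ gain over the tested interval, in SD units, and r the correlation, with equal SDs at both times.

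- SD of the change = √(2(1 − r)): 1.000 for r = 0.5, 0.894 for r = 0.6, 0.775 for r = 0.7.
- Standardised change dz = m / √(2(1 − r)). For r = 0.6 and m = 0.2, 0.3, 0.5 this is 0.224, 0.335, 0.559.
- Rejection probability from the noncentral t with n − 1 degrees of freedom and noncentrality dz√n.

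| Natural gain m | 22 pairs, r = 0.5 | 22 pairs, r = 0.6 | 22 pairs, r = 0.7 | 28 pairs, r = 0.5 to 0.7 |
|---|---|---|---|---|
| 0.2 SD | 15% | 17% | 21% | 18–26% |
| 0.3 SD | 27% | 32% | 41% | 33–51% |
| 0.5 SD | 61% | 71% | 82% | 72–91% |

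The nominal rate is 5%. The rates rise with more participants because the problem is bias, not imprecision.

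**Step 3. How precise is the two-group estimate?** Half-width of the 95% CI in SD units = t × √(2/n). With 22 per group: 2.018 × √(2/22) = 2.018 × 0.3015 = 0.61. If 28 are recruited and 25% are lost, 28 × 0.75 = 21 per group remain, and the half-width is 2.021 × √(2/21) = 0.62.

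**The case against.** The strongest reply is that this is an openly exploratory feasibility study. Section 3 says that its findings are to inform a larger trial and not to settle effectiveness. Section 2.5.1 gives the lack of randomisation as its reason for keeping the group comparison exploratory, which is defensible, and it already plans between-group effect sizes with confidence intervals. The ranking of time points and the list of covariates are commonly left to an analysis plan that is not shown here.

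Much of this stands, and it limits the point in five ways.

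- A reader might infer that the paired test is the only formal effect test. The text does not say so: the words primarily and alone leave between-group testing open. It is the only test *named*.
- A reader might infer that natural change will be reported as a programme effect, or that a false positive is likely. The plan neither calls the paired test primary nor attributes its result to the programme. In Step 2, rejection exceeds one half at 22 pairs only for the largest assumed gain.
- A reader might see the T1 contrast as clean. It is not. Allocation is by age, the listed eligibility criteria differ between groups, and only the intervention group has answered TRAQ before.
- A reader might take the two-group comparison as well powered. It is so only at 1 SD.
- A reader might ask for the questionnaire mode to be changed. Only baseline is on paper and controls have no baseline, so their T1 is by implication electronic already. A change of mode would also alter data collection after the recruitment period given in 2.1 (March 2025 to March 2026).

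What the reply does not answer is the use made of the within-group change. The caution in 2.5.1 is directed at differences between groups. The general caution in section 3 does not mention natural change, and that section still sends preliminary effect sizes forward.

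**Conclusion.** The point holds in this limited form. The sizing and the analysis do not match: 22 per group is a two-sample figure (90% power at d = 1.0, about 49% at 0.6), yet the only named test is an uncontrolled paired one, and the two-group comparison has no stated time point or main estimate. Because controls lack T0 and mode changes with time, the paired change cannot isolate the programme, and natural change *can* be read as an effect.

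The mismatch and the confounding follow from the text alone. Their size does not: the rates of about 15–21%, 27–41% and 61–82% rest on assumed natural gains of 0.2, 0.3 and 0.5 SD, correlations of 0.5–0.7, 22 pairs and no programme effect. The documents do not support saying that a false claim is probable, nor that the between-group comparison is absent or would be free of bias.

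**What to change.** In section 2.5.1:

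1. Name the between-group difference in TRAQ at T1, with its 95% CI, as the main effect estimate, adjusted for condition, sex and age as far as the sample allows. State that it remains exploratory and non-randomised. Make T2 secondary.
2. Describe within-group change as uncontrolled. Say that it will not be attributed to the programme and will not be used alone as the effect size for the future trial. Name natural change and the change of mode as reasons.
3. State once whether IPTW is conditional (2.5.1) or definite (section 3).
4. Reconcile the 1 SD target with the stated effect size below 0.6 in 2.3.2, so that the reader knows which difference the 22 per group can detect.
5. Confirm that the controls' T1 questionnaire is electronic, as 2.3.1 and 2.4.1 together imply. No change of mode is needed.

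**Cost.** The change is one of wording and uses data already planned. Data collection runs to December 2026 and analysis to March 2027 (2.1), so it can be settled before results are known. The drawbacks are a wide interval (about ±0.61 SD at 22 per group) and confounding by age-based allocation, which adjustment may reduce but cannot remove.

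### Paired tests without imputation leave unused the baseline scores of intervention participants lost before T1, which can flatter the T1 group contrast by about 0.05–0.2 SD

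*Protocol article*

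**What the plan says.** Section 2.5.1 fixes the within-group analysis: "Within the intervention group, pre-post changes over time will be evaluated using paired t-tests or non-parametric equivalents when assumptions are not met". On incomplete data it states: "Missing data will be reported and handled transparently; given the expected small sample size, no multiple imputation procedures are planned". For the group comparison it says that "analyses comparing the intervention and control group will primarily be descriptive and exploratory". Inverse probability of treatment weighting is to be explored for baseline differences if feasible, and the emphasis is on effect sizes and confidence intervals.

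Section 2.3.1 gives the intervention group three questionnaires (T0, T1, T2) and the control group two (T1, T2). Section 2.3.2 admits intervention participants at age 17 with "a planned transfer to adult care within 12 months". For controls it reads: "Participants in the control group are aged 17,5–18 years, Dutch-speaking, with a planned transfer to adult care in the near term". The same section expects 25% attrition over 24 months and asks for at least 28 recruits per group.

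Section 2.4.1 has T0 completed on paper with a researcher present. After that the mode changes: "At subsequent time points, questionnaires will be administered electronically via a secure online survey platform". The Discussion (section 3) says the study will supply preliminary effect sizes for a larger evaluation.

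**The concern.** A paired test uses only people who have both scores of the pair. With no imputation and no other method named, a participant who gave T0 and then left contributes nothing to the T0–T1 analysis, and a plain comparison of T1 means ignores that T0 score too. A small sample can be a reason to avoid multiple imputation. It is not a reason to leave observed scores unused, because a likelihood-based model on all observed scores needs no imputation.

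Two estimates are affected, and they must be kept apart.

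- **T1 group contrast.** The intervention group has a longer time at risk before T1. If those who leave are the less ready, its completers look better at T1 than the enrolled group would have.
- **T0–T1 change within the intervention group.** Unequal loss against controls plays no part here. The size and sign of the error depend on what drives the loss.

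The group contrast matters more, since its effect size is to be carried into the design of a later trial.

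**Working it through.** **Inputs from the protocol article.** 28 recruited to the intervention group; 25% attrition over 24 months; up to about 12 months from entry to transfer; T0 in the intervention group only.

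**Assumed, because the article does not give them.** T0–T1 correlation r = 0.4 or 0.6; scores with SD 1; loss before T1 in the intervention group only; log-odds of loss rising by 0.5 or 1 per SD lower score.

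**Counts.** At 25% loss, 28 × 0.75 = 21 pairs remain and 7 observed T0 scores go unused. The 25% is stated for 24 months. Spread at a constant rate, loss by 12 months would be 1 − 0.75^(12/24) = 0.134, or about 4 people. Both rates are shown below.

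**Estimators.** m0 and m1 are the completers' means at T0 and T1, M0 is the T0 mean of everyone enrolled, and b is the completers' regression slope of T1 on T0.

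- Completers: T1 mean = m1; change = m1 − m0.
- Likelihood: T1 mean = m1 + b(M0 − m0); change = that value − M0.

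The second is the maximum-likelihood solution for T0 and T1 with unstructured covariance when T0 is complete. It stands in for the full model with T2 and controls.

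**Hand check, loss driven by T0, slope 1, 25% lost.** Completers' mean T0 is about 0.21–0.22 SD above the enrolled mean.

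- T1 mean overstated by r × that: 0.4 × 0.213 = 0.085; 0.6 × 0.216 = 0.130.
- Change biased by −(1 − r) × that: −0.6 × 0.213 = −0.128; −0.4 × 0.216 = −0.086.

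**Simulation, 20,000 samples of 28 per scenario, 25% lost.** Bias in SD units, range over both correlations and both slopes:

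| Loss driven by | T1 mean, completers | T1 mean, likelihood | Change, paired completers | Change, likelihood |
|---|---|---|---|---|
| observed T0 | +0.05 to +0.13 | 0.00 | −0.05 to −0.13 | 0.00 |
| unseen T1 | +0.12 to +0.21 | +0.08 to +0.18 | +0.05 to +0.13 | +0.08 to +0.18 |
| stable personal trait | +0.08 to +0.17 | +0.04 to +0.08 | 0.00 | +0.04 to +0.08 |

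Precision is practically equal. The SD of the estimated T1 mean is 0.21–0.22 for completers and 0.20–0.22 for likelihood; for the change it is 0.19–0.24 for both.

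**At 13.4% loss.** The completers' T1 mean is overstated by about 0.02 to 0.12 SD across the same scenarios, and by 0.00 to 0.10 SD under likelihood.

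**Reading.** For the T1 mean, likelihood is less biased in every scenario. For the change it is better in the first row and worse in the other two.

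**The case against.** The strongest objection is that the mixed model looks good only if loss depends on observed scores. That stands for the within-group change. When a stable trait drives loss, the paired estimate is unbiased and the likelihood estimate is off by 0.04–0.08 SD in the programme's favour. A paired test needs loss to be unrelated to the change score; the mixed model needs missing at random. Neither condition implies the other. A reader might infer that the mixed model removes the bias at no cost, or rests on a strictly weaker assumption. Neither follows, and the article does not say what drives loss.

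A reader might also infer that only the intervention group can be lost before T1. The article does not support that: controls are enrolled before transfer and receive T1 electronically, so they can fail to return it. If controls were lost in the same proportion and by the same selection, the errors in the observed T1 means would cancel, and correcting the intervention group alone would tilt the contrast against the programme. The gain therefore depends on loss falling mainly in the intervention group. The enrolment windows make that likely but do not prove it.

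The article rules out only multiple imputation, promises transparent handling and calls the group comparison exploratory; a fuller analysis plan may say more. That limits the weight of the point. It does not remove it, because the test is fixed here and the effect sizes are to be reused. Weighting for baseline group differences does not address loss after enrolment.

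Finally, the bias is modest: at most about one SD of the estimator, and up to about a fifth of the 1 SD target in section 2.3.2.

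**Conclusion.** The point holds for the T1 group contrast. Under the stated plan, observed T0 scores are left out in the group with the longer risk of loss. If less-ready participants leave and loss is mainly in that group, its T1 mean is overstated by about 0.05–0.2 SD at 25% loss, or about 0.02–0.12 SD if only 13% are lost by T1. A likelihood model reduced this under all three loss mechanisms examined, with practically equal precision. It removed it only when loss depended on observed T0.

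For the T0–T1 change, neither method is better in general, and the paired test is not an error. The correlations, the strength of selection and the absence of loss in controls are assumptions.

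**What to change.** 1. Estimate the T1 and T2 group differences from one linear mixed model on all observed TRAQ scores (T0, T1, T2 in the intervention group; T1, T2 in controls), with group-by-time means, unstructured within-person covariance, REML and Kenward–Roger degrees of freedom. Use the same model for the secondary scales.
2. For the T0–T1 change, report the mixed-model and paired-completer estimates side by side and state the assumption behind each.
3. Report loss before T1 by group, with T0 scores of those lost and those retained in the intervention group.
4. Add a simple missing-not-at-random analysis: assume that those lost score δ SD below the model's prediction and move the mean by the share lost × δ. For example, 25% lost and δ = 0.5 lowers the T1 mean by 0.25 × 0.5 = 0.125 SD. The range of δ should be set in advance.

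Cost: analysis wording and a little more work, with no new data. The model relies on missing at random and cannot recover controls who give no score at all.
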